# Generalities

SAP:

Statistical analysis will be performed by independent statisticians from PUCRI.

Statistical analysis plan presented below has been written before database lock.

All modifications made to the analysis plan for the initial strategy will be documented in the analysis report.

Software:

Analyses will be performed using SAS software (version 9.4 or updated version).

Planned analyses:

No interim analysis is planned. Analyses will be performed at the end of the study after database lock.

# Trial overview

## Research title

A multicenter, randomized, double-blind, placebo-controlled clinical study of Shensong Yangxin Capsule on prognosis in patients with atrial fibrillation undergoing radiofrequency ablation.

## Objective of the study

Aim to evaluate the effect of Shensong Yangxin Capsule on patients with atrial fibrillation after radiofrequency ablation, to explore more effective clinical treatment methods for these patients, and to provide high-quality clinical evidence for optimizing clinical rational drug use.

## Study Design

A multicenter, randomized, double-blind, placebo-controlled clinical study was adopted in accordance with international norms to evaluate the effect of Shensong Yangxin Capsule on postoperative prognosis of patients with persistent atrial fibrillation after radiofrequency ablation. All patients who were enrolled according to the Chinese Medical Association's《Atrial fibrillation: According to the guidelines of Current Understanding and Treatment Recommendations 2018》, took Shensong Yangxin Capsule or placebo for 1 year on the basis of conventional treatment. and the recurrence rate of patients with atrial fibrillation within 1 year was defined as the primary research endpoint.

## Study Population

Patients must met all of the inclusion criteria listed below, with the exception of any of the exclusion criteria.

### Inclusion Criteria

(1) Age 18-75 years old;

(2) Diagnosed with persistent atrial fibrillation;

(3) History of atrial fibrillation < 5 years;

(4) Radiofrequency ablation for the first time;

(5) Voluntarily participate in this study and have signed informed consent.

### Exclusion criteria

(1) Valvular atrial fibrillation heart disease;

(2) NYHA cardiac function grade Ⅳ or LVEF<40%, LA diameter >50mm;

(3) Moderate to severe left ventricular hypertrophy (wall thickness >1.5cm);

(4) Patients with acute coronary syndrome or patients requiring stent implantation;

(5) Patients with a history of cardiac surgery and catheter ablation in the past 6 months;

(6) History of atrial fibrillation≥5 years;

(7) Hyperthyroidism;

(8) Patients with atrial fibrillation with cardiomyopathy;

(9) Patients with chronic arrhythmia requiring pacemaker installation;

(10) Patients with known bleeding constitution and left atrial/left auricular thrombus or severe hemostasis and coagulation dysfunction;

(11) Severe hepatic and renal insufficiency [ALT≥3 ULN or eGFR<50ml/min/1.7m^2^];

(12) Patients with neuropsychiatric diseases;

(13) Allergic to the ingredients of the study;

(14) Pregnant or lactating women;

(15) Patients who are participating in other clinical studies;

(16) Patients who are deemed unfit by the investigator to participate in this study.

## Sample Size

Referred to《Catheter ablation vs. antiarrhythmic drug treatment of persistent atrial fibrillation: a multicentre, randomized, controlled trial (SARA study)》(European Heart Journal, 2014 Volume 35, Issue 8, Pages 501-507).

Assumed the 1-year recurrence rate of patients with persistent AF after radiofrequency ablation is 39.8% (the duration of an episode of AF/flutter/atrial tachycardia recorded by ECG≥30s 3 months after ablation is considered as a recurrence of AF). We predicted that the 1-year recurrence rate of atrial fibrillation could be reduced to 30% by adding Shensong Yangxin capsule after radiofrequency ablation. Therefore, we may expect that sample size of minimum 368 patients in each study group will provide the study with 80% power to detect a difference in primary outcome at 5% of significance. Accounting for 20% of lost to follow up patients of the trial, we need to include 460 patients in each group and the total sample size is 920.

## Blind method and randomization

Independent biostatistician of Clinical Research Institute of Peking University used SAS9.4 statistical software package to generate random numbers of study drugs by block randomization method on the computer according to the ratio of study group and control group 1:1. And according to this random number, the study drug (Shensong Yangxin capsule or placebo) was packaged and coded by personnels unrelated to the study.

The Randomized and Investigational Drug Management System (RTSM) was used in this study, and the independent biostatistician will provide the RTSM with a list of drug random numbers. Central random method was used in the study. After completing the baseline assessment, investigators were required to log on to RTSM and provide some information (e.g., subject's date of birth, gender, etc.) before randomizing patients if they met the inclusion criteria. The system will generate patient random number and corresponding drug number in order of enrollment time. Each follow-up visit needs to log in the system to apply for a new drug number. The drug number is different, but the drug group is the same.

The second unblinding method was adopted in this study. After the blind state verification, the data was locked, and the main researcher, biostatistician and data administrator conducted the first blind uncover. The corresponding groups of each random number were marked with the code A and B, so as to carry out statistical analysis on all the data. When the statistical analysis was completed and the statistical report was completed, the second unblinding was carried out and the exact groups of the two groups A and B were announced.

## Treatment

**Teat Group:** conventional treatment+ Shensong Yangxin capsule 4 capsules/times, 3 times/day, orally.

**Control Group:** conventional treatment + Shensong Yangxin capsule placebo 4 capsules/times, 3 times/day, orally.

All the above treatments were performed after radiofrequency ablation, and the course of treatment was 1 year

# Endpoints

Efficacy endpoints

### Primary efficacy endpoint

The primary efficacy endpoint was the recurrence rate of atrial fibrillation. The recurrence of atrial fibrillation after ablation was statistically analysed from the following two perspectives

(1) The first recurrence of atrial fibrillation after the 90-day ablation period was used as the primary efficacy endpoint. Among them, the recurrence rate was defined as the duration of atrial fibrillation/flutter/atrial tachycardia recorded by ECG ≥30s from the end of the 3-month blackout period to the end of follow-up, which was considered as the recurrence of atrial fibrillation. The last postoperative follow-up was used as the follow-up endpoint for this analysis. Recurrence of atrial fibrillation during follow-up after surgery was defined as an event, absence of recurrence of atrial fibrillation was defined as censored, and the censored date was defined at the last date of follow-up. Persistent atrial fibrillation was defined as 24 Holter patients with total atrial fibrillation or 2 routine electrocardiograms with an interval of > 7 days, failure to spontaneously recurve, and no sinus rhythm electrocardiograms during hospitalization.

(2) 1-year recurrence of atrial fibrillation from 90 days after ablation to 1 year after surgery was used as the primary efficacy endpoint. Among them, the 1-year recurrence rate of atrial fibrillation was defined as the duration of atrial fibrillation/flutter/atrial tachycardia recorded by ECG ≥30s from the end of the 3-month blackout period to 1 year after surgery, which was considered as atrial fibrillation recurrence. 1 year after surgery was used as the end point of follow-up for this analysis. Recurrence of atrial fibrillation occurring after 1 year was defined censored, and the censored date was 365 days after surgery. Persistent atrial fibrillation was defined as 24 Holter patients with total atrial fibrillation or 2 routine electrocardiograms with an interval of >7 days, unable to spontaneously recurve, and no sinus rhythm electrocardiograms during hospitalization.

With reference to most literatures, the current assessment of recurrence of atrial fibrillation after ablation is mainly based on Holter electrocardiogram (ECG), remote electrocardiogram or the patient's symptoms. In this study, 24h-holter electrocardiogram and electrocardiogram will be used as monitoring means to evaluate recurrence of atrial fibrillation after radiofrequency ablation based on each visit of the patient at the follow-up point and the patient's symptoms.

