# Processing of missing data

In this study, survival analysis was used to analyse the 1-year recurrence of atrial fibrillation for the primary efficacy endpoint. mITT and PPS were both included for the patients who failed to complete the 1-year follow-up due to half-way drop out or missing follow-up. The endpoint was defined as censored in the statistical analysis, and the censored date was the last follow-up date. No carry-over of missing data or multiple fillings of missing data were performed.

Missing data of secondary endpoints and safety endpoints, no filling or other processing is carried out.

Handling of dates: When only part of the date is known, the following rules are used to calculate the duration. If the start time (such as the date of first onset of AF or the date of diagnosis) is partially missing and only the day is missing, then fill in the first day of the corresponding month. If the end date is partially missing and only the day is missing, replace it with the last day of the month. If both the day and month of the date are missing, this date is treated as missing.

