# Statistical analysis Methods

General principles of statistical analysis

Statisticians are responsible for developing a statistical analysis plan (SAP) with the principal investigator after the protocol is confirmed. Statistical analysis will be performed with SAS 9.4 (or higher version; SAS Institute, Cary, NC). The sample size is calculated using PASS13 software (NCSS, Kaysville, UT).

A 2-tailed P<0.05 will be considered statistically significant in all statistical tests. (If no other specification). No adjustments for multiple comparisons were made.

Qualitative data will be described with frequencies and percentages; quantitative data will be described with mean and standard error or with median and interquartile interval, minimum and maximum.

Continuous variables will be summarized with mean and SD and compared using paired t-test or Wilcoxon rank test, as appropriate. Categorical variables will be summarized with frequencies and percentages and compared using chi-square test or Fisher exact test, as appropriate. Ranked variables will be compared using Wilcoxon rank test or CMH test.

Enrolment Analysis

Enrollment analysis will summarize the number of enrollment and the number of subjects who completed the trial of each site and lists dropout subjects.

The dataset size between groups, subjects' disposition between sites, dropout rate and termination reasons will be listed in detail

Baseline and demographic characteristics

Baseline characteristics of patients will be described overall and per group.

Demographic and baseline characteristics (age, gender, height, BMI, vital signs, etc.), medical history, family history of atrial fibrillation, drug allergy, etc. of the subjects will be summarized. T-test or Wilcoxon rank-sum test will be used in baseline comparison of continuous variables such as age, height, and BMI between the two groups. The chi-square test or Fisher’s exact test will be used in the baseline comparison of categorical variables such as gender, and medical history

Analysis of efficacy

Both mITT and PPS were used for effectiveness analysis. Analysis performed on PP populations using the same methods can be considered as a sensitivity analysis.

(1) Baseline: The baseline of each relevant efficacy endpoints was described. For comparison methods between groups, refer to the general statistical method above.

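### SAP section 3.1.1 labels two different analyses as primary, tests both at 5% without order or decision rule, and conflicts with the 1-year endpoint used elsewhere in the SAP

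*SAP*

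**What the plan says.** Section 3.1.1 (Primary efficacy endpoint) introduces a single quantity, the recurrence rate, and continues: "The recurrence of atrial fibrillation after ablation was statistically analysed from the following two perspectives". Both items in the list then receive the primary label.

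- Item (1): "The first recurrence of atrial fibrillation after the 90-day ablation period was used as the primary efficacy endpoint". Its window has no fixed end: "The last postoperative follow-up was used as the follow-up endpoint for this analysis".
- Item (2): "1-year recurrence of atrial fibrillation from 90 days after ablation to 1 year after surgery was used as the primary efficacy endpoint". Its window is closed: "1 year after surgery was used as the end point of follow-up for this analysis".

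Section 6.4 (Analysis of efficacy) applies the same log-rank test and Cox model to both and ranks neither. It codes a recurrence after 1 year as an event in (1) and as censored in (2). Section 6.1 sets two-sided P<0.05 for all tests unless otherwise specified, and adds: "No adjustments for multiple comparisons were made".

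Other sections refer to the 1-year endpoint only. Section 2.3 (Study Design) says that "the recurrence rate of patients with atrial fibrillation within 1 year was defined as the primary research endpoint". Section 2.5 (Sample Size) compares 1-year rates of 39.8% and 30%. Section 5 says that "survival analysis was used to analyse the 1-year recurrence of atrial fibrillation for the primary efficacy endpoint". Section 2.7 gives a 1-year treatment course.

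**The concern.** The two analyses are not two displays of one result. They differ in follow-up window and in the coding of any patient whose first recurrence comes after 1 year, so their P values and hazard ratios can differ. Analysis (1) also counts events after the treatment course has ended, which is a different question from the one the trial was sized to answer.

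Two things are at stake. The larger is the missing decision rule: if one analysis gives P<0.05 and the other does not, the SAP does not say whether the trial succeeded. The smaller is type I error: if either result may be claimed, the chance of a false positive is above the stated 5%.

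**Working it through.** **1. The plan's own figure.** Inputs from section 2.5: recurrence 39.8% and 30%, 5% significance, 80% power, 20% loss. With the unpooled two-proportion formula and a two-sided test:

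n = (1.960 + 0.842)² × (0.398 × 0.602 + 0.30 × 0.70) / (0.398 − 0.30)² = 7.849 × 0.4496 / 0.009604 = 367.4, rounded up to 368 per group.

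368 / 0.80 = 460 per group, 920 in total. The stated figures reproduce. They rest on one comparison of 1-year rates at a full 5%, which corresponds to analysis (2) alone.

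**2. Type I error if either analysis may be claimed.** Every event in (2) is also an event in (1). Let s be the share of the events in (1) that occur by 1 year. Under the null, the two log-rank statistics are approximately bivariate normal with correlation ρ = √s, and

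P(at least one P<0.05) = 1 − P(|Z₁| ≤ 1.96 and |Z₂| ≤ 1.96).

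The SAP does not give s, so a range is assumed.

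| Events after 1 year (assumed) | ρ | Type I error, either may be claimed |
| --- | --- | --- |
| 1% | 0.995 | 5.5% |
| 5% | 0.975 | 6.0% |
| 10% | 0.949 | 6.5% |
| 20% | 0.894 | 7.1% |

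For comparison, two independent tests would give 1 − 0.95² = 9.75%. That ceiling does not apply here, because the tests share all events up to 1 year.

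**3. How often the two analyses would disagree.** Under exponential recurrence, the planned rates imply a hazard ratio of ln(0.70)/ln(0.602) = 0.703. Schoenfeld's formula then gives 253 events for 80% power. The mean of Z₂ is √253/2 × 0.353 = 2.80. The mean of Z₁ is 2.80/√s if the effect persists after 1 year, and 2.80 × √s if it stops at 1 year. The chance that the two tests fall on opposite sides of P=0.05 is then:

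| Events after 1 year (assumed) | Effect persists | Effect stops at 1 year |
| --- | --- | --- |
| 10% | 7.4% | 8.3% |
| 20% | 11.0% | 13.8% |

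**4. Cost of the alternatives.** One primary analysis at 5%, or a fixed order, leaves 368 per group unchanged. Keeping both as alternative primaries with Bonferroni at 0.025 each needs 449 per group with the pooled formula (371 at 5% by that formula). After 20% loss this is 562 per group, 1,124 in total. At 368 per group, power would fall from 79.8% to 70.9%.

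**5. Definition of analysis (2).** Section 3.1.1 censors recurrences after 1 year at 365 days after surgery. Section 6.4 measures time from ablation + 90 days, adding 1, so day 365 after surgery is 365 − 90 + 1 = 276 on that clock. Yet section 6.4 sets the censoring time at 365 days for patients without recurrence, and at the last visit on the day-90 clock for patients who recur after 1 year. The three rules do not agree.

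**The case against.** Several points on the other side are fair.

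- **The document leans towards one analysis.** Section 3.1.1 opens with a single endpoint, and sections 2.3, 2.5 and 5 all favour (2). A reader might infer that the plan has no primary endpoint at all, but the text does not support that. What stands is an internal contradiction: the section that defines the endpoint lists the open-ended analysis first and calls it primary, and nothing says the other sections override it.
- **The SAP never says that either result suffices.** A reader might infer that the trial certainly has two chances of success, or that its error rate is near 10%. Neither follows. If both analyses had to succeed, error would not exceed 5%. Even if either may be claimed, the shared events keep the inflation modest: about half a percentage point if only 1% of events are late.
- **Follow-up beyond 1 year is not an error in itself.** A reader might infer that late data in (1) depend on who happens to attend. The SAP does not show the visit schedule, and (1), the time to first flutter or fibrillation, and adverse events are not limited to 1 year. Scheduled later visits are possible, so that inference is unsupported.
- **The numbering might be read as a hierarchy.** It is a list, and no testing order is stated.

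The mITT and per-protocol analyses add no further route to success: section 4 makes mITT primary, and section 6.4 allows per-protocol as a sensitivity analysis.

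**Conclusion.** The point holds and should be corrected: as written, the SAP does not fix which analysis decides the trial, and section 3.1.1 contradicts sections 2.3, 2.5 and 5. This rests on the text alone and needs no assumption.

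The inflation to about 5.5% to 7.1% is conditional. It requires that either analysis may be claimed and that 1% to 20% of events fall after 1 year. The disagreement rates further assume the planned effect and about 253 events by 1 year. The missing decision rule, more than the size of the inflation, is the reason to act.

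**What to change.** In section 3.1.1, name analysis (2), day 90 to 1 year after ablation on the mITT set, as the sole primary analysis on which the trial's conclusion rests. Make analysis (1) supportive with a nominal P value, or test it at 5% only after (2) is significant, in a stated fixed order. Either option holds type I error at 5% across the two analyses.

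In the same revision, reconcile the censoring of analysis (2) between sections 3.1.1 and 6.4. State one time origin, and one censoring time on that clock for every patient without a recurrence by 1 year, so that the sole primary has one definition.

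The sample size stays at 368 per group, 920 in total after loss. The change is to SAP wording; whether the protocol needs a matching edit cannot be judged from the SAP alone. The small downside is the loss of an independent second route to a positive claim.

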### Secondary efficacy endpoints

(1) Changes in atrial fibrillation load at 3 months, 6 months, and 1 year after treatment. Atrial fibrillation load was defined as the longest duration of atrial fibrillation episodes, the number of episodes of atrial fibrillation, and the percentage of time patients were in atrial fibrillation during a given monitoring period.

(2) Time of first occurrence of atrial flutter/atrial fibrillation.

(3) Incidence of electrical cardioversion within 1 year after treatment.

(4) Changes of transthoracic echocardiographic indexes at 1 year after treatment.

(5) Incidence of stroke and thromboembolism at 6 months and 1 year after treatment.

(6) Health Survey Summary Form (SF-36) score within 1 year after treatment.

Safety endpoints

(1) Adverse events (AEs): Any adverse medical events occurring between the time subjects signed the informed consent and were enrolled in the study and the last follow -up, regardless of whether there was a causal relationship with the study drug, was considered an adverse event. The sum of "definitely relevant", "possibly relevant" and "unascertainable" associated with the study drug was the adverse reactions (ADRs) of the study drug, and the incidence of adverse reaction was calculated accordingly.

(2) Laboratory indicators: blood routine, urine routine, stool routine, biochemical examination and coagulation function examination;

(3) Clinical physical examination and vitals.

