Aimed at changes in atrial fibrillation load at 3 months, 6 months and 1 year after treatment, the mean, standard deviation, median, minimum, maximum, lower quartile (Q1) and upper quartile (Q3) of atrial fibrillation load at each visit site were calculated according to the form of quantitative endpoints. T-test or Wilcoxon rank sum test were used to compare it between the two groups. At the same time, the changes of atrial fibrillation load compared with baseline at 3 months, 6 months and 1 year after treatment were statistically described, and T-test or Wilcoxon rank sum test was used to compare the changes between the two groups.

The time of the first occurrence of atrial fibrillation/atrial fibrillation was analysed as the secondary endpoint. The occurrence days of atrial fibrillation/atrial fibrillation were calculated by the date of radiofrequency ablation surgery as the starting date, the occurrence days= the date of the first occurrence of atrial fibrillation/atrial fibrillation-the date of radiofrequency ablation surgery +1. For patients with atrial flutter/atrial fibrillation, the mean, standard deviation, median, minimum, maximum, lower quartile (Q1) and upper quartile (Q3) of occurrence time were calculated according to the form of quantitative variables. T-test or Wilcoxon rank sum test were used to compare the occurrence time between the two groups.

The secondary efficacy endpoint of transthoracic echocardiography one year after treatment were analysed. The indexes of transthoracic echocardiography mainly included left ventricular end-diastolic volume, left ventricular end-systolic volume, ejection fraction, stroke volume, cardiac output and other evaluation indexes. The mean, standard deviation, median, minimum, maximum, lower quartile (Q1) and upper quartile (Q3) of the results of the evaluation indicators were calculated according to the form of quantitative variables, and T-test or Wilcoxon rank sum test were used to compare the evaluation variables between the two groups.

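### Comparing the number of AF episodes as a plain quantity ranks whole-recording AF better than two brief runs, which weakens this component of AF load as a measure of benefit

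*SAP*

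**What the plan says.** SAP section 3.1.2 lists as the first secondary efficacy endpoint "Changes in atrial fibrillation load at 3 months, 6 months, and 1 year after treatment". It defines load by three descriptors: "Atrial fibrillation load was defined as the longest duration of atrial fibrillation episodes, the number of episodes of atrial fibrillation, and the percentage of time" in AF within a monitoring period.

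Section 6.4 summarises mean, SD, median, quartiles and range "of atrial fibrillation load at each visit site were calculated according to the form of quantitative endpoints", and then "T-test or Wilcoxon rank sum test were used to compare it between the two groups". For change, "the changes of atrial fibrillation load compared with baseline at 3 months, 6 months and 1 year after treatment were statistically described", with the same two tests between arms. Section 6.1 says only that the test is chosen as appropriate.

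Section 2.4.1 requires patients to be "Diagnosed with persistent atrial fibrillation". Section 3.1.1 gives the meaning: "Persistent atrial fibrillation was defined as 24 Holter patients with total atrial fibrillation or 2 routine electrocardiograms" more than 7 days apart, without spontaneous conversion and with no sinus-rhythm ECG in hospital.

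The SAP does not say how AF filling the whole recording is counted, which of the three descriptors is the tested variable, or how to read them if they disagree.

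**The concern.** A between-arm test on a quantity assumes that a larger value is consistently worse. The episode count meets this between no AF and some AF, and between few and many short runs. It fails at the severe end, because AF that never stops is a single episode. In a persistent-AF population that is a main form of relapse, not a rare exception.

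The most affected patients are therefore placed between those with no AF and those with two or more brief runs. At stake is a listed efficacy comparison that dilutes a real benefit and may disagree with the other two components, with no rule for reading the disagreement. The result can also depend on whether the t-test or Wilcoxon is used, and the SAP leaves that open.

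**Working it through.** **The plan's own figure.** Section 2.5 gives 39.8% versus 30%, two-sided 5%, 80% power. With unpooled variance, n = (1.960 + 0.842)² × (0.398×0.602 + 0.30×0.70) / 0.098² = 7.849 × 0.4496 / 0.009604 = 367.4, so 368 per arm. Then 368 / 0.80 = 460 per arm and 920 in total. The stated size is reproduced, and 368 per arm is used below. The SAP gives no figures for AF load, so every split of relapses into continuous and intermittent AF below is an assumption.

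**Two patients on a 24-hour (1,440-minute) recording.** This step needs no assumed mix, only that unbroken AF counts as one episode.

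| | Episodes | Longest | Time in AF |
|---|---|---|---|
| AF throughout | 1 | 24 h | 100% |
| Two 5-minute runs | 2 | 0.083 h | 10/1,440 = 0.69% |

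The count ranks the first patient better; the other two components rank that patient far worse.

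**Group means.** Let c be the proportion in continuous AF, s the proportion with short runs, and k the mean number of runs among the latter. Mean count = c + s×k. It rises under treatment only if the increase in s, times k, exceeds the fall in c. If s does not rise, the mean count cannot rise when c falls.

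**Scenarios with k = 4** (runs drawn as 1 + Poisson(3); burden in intermittent patients uniform 1–20%, mean 10.5%; control c = 25%, s = 14.8%, so control mean count = 0.25 + 0.148×4 = 0.842):

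| Treated arm | Mean count | t-test against drug | Wilcoxon against drug | Wilcoxon for drug |
|---|---|---|---|---|
| A. c = 10%, s = 20% (relapses fewer and shorter) | 0.10 + 0.20×4 = 0.900 | 6.5–7.75% | about 0% | about 43% |
| B. Recurrence 30%, control mix kept | 0.842 × 30/39.8 = 0.635 | 0% | 0% | 79% |
| C. c = 15.2%, s = 14.8% (only continuous AF falls) | 0.152 + 0.592 = 0.744 | 0.15% | 0% | – |

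These rest on 2,000 to 3,000 simulated trials each. About 2.5% significant results in the wrong direction would be expected by chance if there were no difference.

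In A, mean time in AF is 25 + 0.148×10.5 = 26.6% in control and 10 + 0.20×10.5 = 12.1% in treated. The t-test on it favours the drug in over 99% of trials. Wilcoxon on the count with whole-recording AF ranked worst shows benefit in about 95%. The like-for-like loss from the raw count is therefore about 43% against about 95%, same test and same data.

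**When the mix does not change.** With a 50/50 mix in both arms and recurrence falling from 39.8% to 30%, Wilcoxon shows benefit in 74–81% of trials on the raw count and in 74–81% on percentage of time (k = 2, 3, 5; 300 trials each). Nothing is lost here.

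**When the drug only converts continuous AF to short runs.** Any AF is 39.8% in both arms and c falls from 25% to 15%. Mean count rises from 0.546 to 0.646 (k = 2), 0.694 to 0.894 (k = 3) or 0.990 to 1.390 (k = 5). The t-test on the count is significant against the drug in 31%, 56% and 74% of trials, and Wilcoxon in 11–18%. The t-test on percentage of time favours the drug in 89–94%.

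**The case against.** A reader might infer that the plan will make a helpful drug look harmful. The documents do not support that. The only effect the SAP assumes is fewer recurrences, 39.8% to 30%, and under that effect alone the count falls and gives no false signal of harm. Substantial apparent harm needs recurrence to stay equal while continuous AF turns into short runs, which the SAP nowhere anticipates. Even in scenario A, more than nine trials in ten show no significant harm by t-test, and Wilcoxon, the natural choice for a count with 60–70% zeros, shows essentially none. This stands, and it limits the point to lost sensitivity and unclear reading.

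A second tempting inference is that change from baseline is biased because every patient starts at one episode and 100% of time. That does not hold either. Subtracting a constant leaves the between-arm test unchanged, so the comparison would be redundant, not wrong. Nor is a constant baseline established: the SAP does not date the AF-load baseline, and section 3.1.1 also admits patients on two routine ECGs without a full-AF Holter.

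It can also be said that the three components would be reported side by side, so a divergence would be visible, and that the protocol may specify how load is measured. Visibility helps, but a reader would still have no rule for the conflict. Defining the variable that is tested is the SAP's task.

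**Conclusion.** The point holds in a limited form. Section 6.4 compares load as a quantity, the count is one of its components, and the count misorders patients in AF throughout the recording. The misordering is arithmetic. Its effect on the trial depends on how relapses divide between continuous and intermittent AF, which the documents do not give. It ranges from no loss, if the drug only prevents recurrence, through about 43% against 95% power for Wilcoxon under scenario A, to a frequent result in the wrong direction if recurrence is unchanged and relapses only become shorter.

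The conclusion rests on three readings that the SAP does not state but that are natural: unbroken AF counts as one episode, fewer episodes is taken as better, and load is read from the 24-hour Holter. Longest duration and percentage of time order patients correctly. The primary endpoint is unaffected.

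**What to change.** In sections 3.1.2 and 6.4, name percentage of recorded time in AF as the AF load variable for the between-arm test at 3 months, 6 months and 1 year, with longest episode duration as supportive. Report the number of episodes descriptively, with patients in AF for the whole recording shown as a separate category. If the count is to be tested, specify Wilcoxon with whole-recording AF ranked as the worst value. The change-from-baseline comparison need not be removed; at most it is redundant.

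This costs SAP wording only and needs no new data. The downside is that the raw count, one of the three listed descriptors, is no longer formally compared.
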